**Table 2 Vaccination and Dose Escalation Schedule\***

| Week | Vaccination 1                                                            | Vaccination 2                                                            | Vaccination 3                                                            | Vaccination 4                                                                                           |
|------|--------------------------------------------------------------------------|--------------------------------------------------------------------------|--------------------------------------------------------------------------|---------------------------------------------------------------------------------------------------------|
| 0    | n=2:
8 ug Pfs25-EPA/
Alhydrogel ®
(Group 1a)  |                                                                          |                                                                          |                                                                                                         |
| 1    | n=3:
8 ug Pfs25-EPA/
Alhydrogel ®
(Group 1a)  |                                                                          |                                                                          |                                                                                                         |
| 2    | n=5:
16 ug Pfs25-EPA/
Alhydrogel ®
(Group 1b) |                                                                          |                                                                          |                                                                                                         |
| 3    | n=5:
47 ug Pfs25-EPA/
Alhydrogel ®
(Group 2)  |                                                                          |                                                                          |                                                                                                         |
| 4    | n=15:
47 ug Pfs25-EPA/
Alhydrogel ®
(Group 2) |                                                                          |                                                                          |                                                                                                         |
| 8    |                                                                          | n=5:
8 ug Pfs25-EPA/
Alhydrogel ®
(Group 1a)  |                                                                          |                                                                                                         |
| 10   |                                                                          | n=5:
16 ug Pfs25-EPA/
Alhydrogel ®
(Group 1b) |                                                                          |                                                                                                         |
| 12   |                                                                          | n=20:
47 ug Pfs25-EPA/
Alhydrogel ®
(Group 2) |                                                                          |                                                                                                         |
| 20   |                                                                          |                                                                          | n=20:
47 ug Pfs25-EPA/
Alhydrogel ®
(Group 2) |                                                                                                         |
| 26   |                                                                          |                                                                          |                                                                          | n=20:
47 ug Pfs25-EPA/
Alhydrogel ®
(Group 2 +/- Group 1
high responders) |

\*Schedule is approximate; a minimum of 5 days will separate the last subjects vaccinated at the previous dose group from the first vaccinated in the subsequent dose group.

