| Study Population:                          | Malaria-naïve US adults                                                                                                                                                                                                                                                                                                                                                                                 |
| Accrual Period:                            | Approximately September 2011                                                                                                                                                                                                                                                                                                                                                                            |
| Study Design:                              | Dose escalating, open label, Phase 1 clinical trial.
1. Group 1a: n=5, to receive 8 µg Pfs25-EPA/Alhydrogel ® on D0, D56 +/- D300
2. Group 1b: n=5, to receive 16 µg Pfs25-EPA/Alhydrogel ® on D0, D56 +/- D300
3. Group 2: n=20, to receive 47 µg Pfs25-EPA/Alhydrogel ® on D0, D56, D120 and D300

Enrollment will be staggered for additional safety |
| Study Duration:                            | Start Date: Approximately September 2011
End Date: Approximately September 2013
Study participants will be enrolled for a total of 60 or 96 weeks, depending on vaccination schedule (12 months follow-up after the last vaccination)                                                                                                                                                             |
| Study Agent/
Intervention Description: | Pfs25-EPA: Recombinant Pfs25 is expressed in Pichia pastoris . Recombinant EPA, a mutant, non-toxic protein corresponding to sequence of ExoProtein A of Pseudomonas aeruginosa , is expressed in E. coli . Pfs25                                                                                                                                                                  |

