**Table 1 Phase 1 Study of Pfs25-EPA Conjugates in US Healthy Adults**

| Group | N  | Vaccine                                 | Schedule (month)  |
|-------|----|-----------------------------------------|-------------------|
| 1a    | 5  | 8 µg Pfs25-EPA/Alhydrogel ®  | 0, 2, optional 10 |
| 1b    | 5  | 16 µg Pfs25-EPA/Alhydrogel ® | 0, 2, optional 10 |
| 2     | 20 | 47 µg Pfs25-EPA/Alhydrogel ® | 0, 2, 4, 10       |

Groups 1a and 1b are sized for safety rather than immunogenicity, as the higher dose is expected to be necessary for an adequate immune response. Participants in Group 2 will receive 4 doses of vaccine to allow estimation of the effect of the additional dose of vaccine on immunogenicity. A fourth dose was added to explore if a booster dose will increase antibody responses, as preliminary results suggest that antibody responses increase with each of the first 3 doses. In addition, subjects of Group 1a and Group 1b who were exceptionally high (>500 EU) anti-Pfs25 antibody producers as measured by ELISA assay after the second dose will be offered the opportunity to receive a booster dose at 10-11 months. The purpose of this is to obtain high-titer antibodies and evaluate whether transmission blocking activity correlates with the antibody titers. Table 2 shows the vaccination and dose escalation schedule for the 2 groups; first vaccinations within dose groups are staggered for assessment of safety of the vaccine in a small number of subjects in each dose group prior to further enrollments.

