## **6.2 Assignment to Groups**

Subjects in Group 1a will be enrolled first, followed by Group 1b, and Group 2. (Note: subjects in Group 2 were initially randomly assigned to a 2 or 3 dose vaccination schedule (Group 2a or 2b); the protocol was subsequently amended (Version 3) such that all subjects in Group 2 receive 3 doses of vaccine). The protocol was again amended (Version 4) so that the subjects in Group 2 can receive an additional booster 6-8 months later if they received at least 2 previous doses of the vaccine, and so that subjects in Group 1 can also receive the booster 8-9 months later if they had an exceptionally high antibody titer response to the first 2 doses (>500 EU).

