**Study Day 270 ±14 Days**

1. Obtain informed consent for Version 4, if subject is willing.
2. Perform directed history and assessment of any physical complaint.
3. Record vital signs.
4. Obtain blood for CBC with differential and platelet count.
5. Obtain urine for dipstick testing.
6. For females, obtain urine for  $\beta$ -hCG testing.
7. Obtain blood for anti-Pfs25 ELISA.

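### Table 2's Vaccination 4 row is about 20 weeks too early for the Day 300 booster and lists Group 1 high responders under 47 µg, against 8 or 16 µg in the Summary and Table 1

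*Protocol*

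**What the plan says.** **Table 2 (Section 3.1).** The Vaccination 4 column has one entry, at week 26, six weeks after the week-20 entry for Vaccination 3. It reads n=20, 47 µg, "Group 2 +/- Group 1" high responders. A footnote calls the schedule approximate.

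**Timing elsewhere.** Table 1 gives "0, 2, optional 10" for Groups 1a and 1b, and months 0, 2, 4 and 10 for Group 2. The text below Table 1 says that high responders in Group 1 "will be offered the opportunity to receive a booster dose at 10-11 months". Section 6.2 gives intervals: "subjects in Group 2 can receive an additional booster 6-8 months later" and "subjects in Group 1 can also receive the booster 8-9 months later". Section 6.4 fixes the visit at Day 300 ±14 days, about 6 months after dose 3 in Group 2. Appendix B has the booster at Day 300 in both booster schedules.

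**Consent.** At Day 270, Section 6.4 has staff "Obtain informed consent for Version 4, if subject is willing". Appendix B shows the same Day 270 consent for Group 1 high responders.

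**Dose elsewhere.** The Summary has "Group 1a: n=5, to receive 8 µg Pfs25-EPA/Alhydrogel" on Day 0, Day 56 and optionally Day 300, and 16 µg on the same days for Group 1b. Table 1 puts the optional month-10 dose in the 8 µg and 16 µg rows. Sections 5.2, 6.2 and 6.4 and Appendix B do not state a Group 1 booster dose.

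**The concern.** Table 2 is the protocol's vaccination and dose-escalation schedule in a first-in-human trial. A wrong week in it is untidy. A dose that disagrees with two other places is more serious, because all three dose levels come from the same 78 µg/mL vial and only the drawn volume separates them. Someone preparing a Group 1 booster from Table 2 would draw 0.6 mL. Someone working from the Summary or Table 1 would draw 0.1 or 0.2 mL. The protocol does not say which text prevails.

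**Working it through.** **1. Establish the clock of Table 2.** Inputs: first-dose weeks from Table 2 (Group 1a weeks 0-1, Group 1b week 2, Group 2 weeks 3-4) and study days from Section 6.4 (Day 56, Day 120, Day 300). Rule: calendar week = week of first dose + study day / 7.

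| Entry | Calculation | Result | Table 2 |
|---|---|---|---|
| Group 1a, dose 2 | 0 or 1 + 56/7 | 8.0-9.0 | 8 |
| Group 1b, dose 2 | 2 + 56/7 | 10.0 | 10 |
| Group 2, dose 2 | 3 or 4 + 56/7 | 11.0-12.0 | 12 |
| Group 2, dose 3 | 3 or 4 + 120/7 | 20.1-21.1 | 20 |
| Group 2, booster | 3 or 4 + 300/7 | 45.9-46.9 | 26 |

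The rule reproduces every earlier row to within about a week and fails only on the last.

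**2. Size of the timing gap.** For Group 2, 45.9 - 26 = 19.9 and 46.9 - 26 = 20.9, so about 20 weeks. Applying the ±14-day window to Day 300 gives weeks 43.9-48.9, still far from 26. The interval from dose 3 to the booster is (26 - 20) × 7 = 42 days in Table 2, against 300 - 120 = 180 days by study day.

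**3. Where Group 1 belongs.** At Day 300: Group 1a 0 or 1 + 42.9 = week 42.9-43.9; Group 1b 2 + 42.9 = week 44.9. If given at 11 months (11 × 30.44 = 335 days, or 47.8 weeks), the range is week 47.8-49.8.

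**4. A possible origin of the 26.** (300 - 120)/7 = 25.7 weeks, so 26 may be the interval after dose 3 (20 + 26 = 46). This is an inference. The Week column counts from the start of the trial, and nothing marks this row as different.

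**5. Could week 26 happen in practice?** On the subjects' own clocks, week 26 is Day 154-161 in Group 2, from (26 - 4) × 7 and (26 - 3) × 7. In Group 1 it is Day 168-182, from (26 - 2) × 7 and 26 × 7. The Day 270 consent would then be 109-116 days away in Group 2 and 88-102 days away in Group 1.

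**6. The dose contradiction.** Inputs from Sections 1.2.2 and 5.2:

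| Volume | Conjugated Pfs25 | Alhydrogel |
|---|---|---|
| 0.1 mL | 8 µg | 160 µg |
| 0.2 mL | 16 µg | 320 µg |
| 0.6 mL | 47 µg | 960 µg |

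Ratio of the two readings: Group 1a 0.6/0.1 = 6 (Alhydrogel 960/160 = 6); Group 1b 0.6/0.2 = 3 (960/320 = 3).

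**7. Subjects concerned.** Groups 1a and 1b have 5 + 5 = 10 subjects. Only those above 500 EU after dose 2 who accept the offer are boosted, so 10 is the ceiling. The n=20 in the cell equals Group 2 alone and leaves no count for them.

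**The case against.** The strongest reply is that neither slip would mislead anyone running the trial.

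- **Timing.** The Summary, Table 1 and every visit schedule agree on Day 300 or month 10, and consent for the booster is taken at Day 270. This stands. A reader might infer from Table 2 that a booster six weeks after dose 3 was a real prospect; the procedures in Section 6.4 and Appendix B do not support that.
- **Dose.** The Summary and Table 1 agree with each other, and n=20 suggests that 47 µg describes Group 2, with high responders added only to show when they are boosted. This makes 8 or 16 µg the better supported reading, but it does not remove the conflict. The cell names Group 1 under 47 µg. Section 3.1 also says that the Group 1 booster is meant to yield high-titer antibodies, and that the higher dose is expected to be needed for an adequate response, so 47 µg is not absurd on its face.
- **Silence in Sections 5.2 and 6.4.** Section 6.4 uses the same bare instruction to vaccinate at every vaccination visit, and Section 5.2 assigns no group to any volume. That silence is not an error in itself. It matters here only because nothing there resolves the conflict.
- **The Vaccination 4 heading.** That the booster is Group 1's third dose is already clear from Sections 6.4 and 11.3.

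**Conclusion.** The row is wrong as written and should be corrected. Week 26 is about 20 weeks too early for Group 2, taking the Week column to count from the first vaccination in the trial, as the other rows do. The dose for Group 1 high responders is contradictory by a factor of 6 (1a) or 3 (1b) in drawn volume, for at most 10 subjects. The documents do not show which dose was intended.

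A reader might infer more, and the protocol does not support it:

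- 47 µg is not an untested level, since Group 2 receives it up to four times.
- The dose-effect test uses antibody 2 weeks after dose 2, so the booster cannot affect it.
- The adverse-event comparison in Section 11.2 concerns the proportion of subjects with an event, by schedule or dose group, and the listing is by vaccine allocation. Each subject has one allocated group, so the table error does not by itself undermine that analysis.
- Section 13.1 already requires the treatment and doses received to be recorded, so no gap in exposure data follows.
- The Summary gives only approximate dates, and the dose-3 window and the 6-8 month interval let the booster move. How many boosters came before the current version cannot be settled from the document.

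**What to change.** In Table 2, change the Vaccination 4 week for Group 2 to about 46-47 and keep n=20 at 47 µg for Group 2 only. Give Group 1 high responders a separate entry, as their third dose, at Day 300 (month 10-11), with 8 µg / 0.1 mL for Group 1a and 16 µg / 0.2 mL for Group 1b. If 47 µg was intended for them, amend the Summary and Table 1 to say so instead. In either case, state the Group 1 booster dose once at the Day 300 visit in Section 6.4.

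The cost is one table row and one line of text, by amendment or clarification. Visits, sample size and analyses do not change.

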## **3.2 Study Endpoints**

### **3.2.1 Primary Endpoints**

The incidence and severity of systemic and local AEs

### **3.2.2 Secondary Endpoints**

1. Antibody levels elicited by Pfs25-EPA, as measured by ELISA
2. Transmission blocking activity (TBA) of induced antibody as measured in standard membrane feeding assays (SMFA), and correlation of TBA with antibody levels

### **3.2.3 Exploratory Endpoints**

1. T-cell responses to Pfs25 as measured by cytokine levels and ELISPOT assays
2. The number and proportion of Pfs25 specific memory B cells will be measured by flow cytometry and ELISPOT assays

## **3.3 Sample Size and Estimated Duration of Study**

A total of 30 subjects will be vaccinated in this trial. Each subject will be monitored actively for approximately 12 months after the last injection, for a total of 60 or 100 weeks, depending on the vaccination schedule. Up to 100 volunteers will be screened to accommodate possible screening failures.

## **4 Study Population**

### **4.1 Description of Population and Site**

The study will be conducted at the Johns Hopkins Bloomberg School of Public Health, Center for Immunization Research (CIR) in Baltimore, Maryland. CIR has successfully conducted 4 previous Phase 1 studies of malaria vaccine candidates in collaboration with LMIV. Malaria-naïve volunteers will be recruited from the surrounding community through a screening protocol as described in **Section 4.2**.

### **4.2 Recruitment**

Healthy adult male and non-pregnant female volunteers will be recruited from a variety of sources including those previously screened or enrolled in other vaccine trials at the CIR, or by the use of an Institutional Review Board (IRB)-approved screening protocol and study-specific print or media advertising. After an initial phone screen (using an IRB approved Phone Screen/Initial Contact form) by clinic staff consisting of providing background information of the trial and a review of basic inclusion and exclusion criteria, a screening visit will be scheduled.

During the screening process, which may require more than one visit, the volunteer will read the consent form, be encouraged to ask questions, and then complete a written comprehension evaluation questionnaire ([Appendix A](#)). The questionnaire is used to identify the areas of the

study and consent that the volunteer may not fully understand. The person administering consent reviews the answers with the volunteer. If the volunteer gets a question wrong, the person administering the consent reviews the portion of the consent form that relates to that particular question with the volunteer. The volunteer may either sign the consent form during the screening visit, or return after further consideration.

### **4.3 Inclusion Criteria**

All of the following criteria must be fulfilled for a volunteer to participate in this trial:

1. Age between 18 and 50 years.
2. Good general health as a result of review of medical history and/or clinical testing at the time of screening.
3. Available for the duration of the trial.
4. Willingness to participate in the study as evidenced by signing the informed consent document.
5. If female: subject is willing to use reliable contraception methods for the period of at least 1 month (2 months for oral contraceptive pills) prior to first vaccination to 3 months after last vaccination. Reliable methods of birth control include: pharmacologic contraceptives including oral, parenteral, and transcutaneous delivery; condoms with spermicide; diaphragm with spermicide; surgical sterilization; vaginal ring; transdermal patch; intrauterine device; abstinence; and post-menopause.

### **4.4 Exclusion Criteria**

A volunteer will be excluded from participating in this trial if any one of the following criteria is fulfilled:

1. Pregnancy as determined by a positive urine or serum human choriongonadotropin ( $\beta$ -hCG) test at any point during the study (if female).
2. Currently is lactating and breast-feeding (if female).
3. Behavioral, cognitive, or psychiatric disease that in the opinion of the investigator affects the ability of the participant to understand and cooperate with the study protocol.
4. Neutropenia as defined by an absolute neutrophil count  $<1500/\text{mm}^3$ .
5. Alanine transaminase (ALT) level above the laboratory-defined upper limit of normal.
6. Evidence of clinically significant neurologic, cardiac, pulmonary, hepatic, endocrine, rheumatologic, autoimmune, hematological, or renal disease by history, physical examination, and/or laboratory studies including urinalysis.
7. Other condition that in the opinion of the investigator would jeopardize the safety or rights of a participant participating in the trial or would render the subject unable to comply with the protocol.

8. History of receiving any investigational product within the past 30 days.
9. Receipt of antimalarial prophylaxis during the past 12 months, or planned travel to a destination which would require malaria prophylaxis during the period of participation.
10. Prior malaria infection by history.
11. Participant has had medical, occupational, or family problems as a result of alcohol or illicit drug use during the past 12 months.
12. History of a severe allergic reaction or anaphylaxis.
13. Severe asthma. This will be defined as:
  - Asthma that is unstable or required emergent care, urgent care, hospitalization or intubation during the past 2 years, or that requires the use of oral or parenteral corticosteroids.
  - Clinically significant reactive airway disease that does not respond to bronchodilators.
14. Positive ELISA and confirmatory Western blot tests for HIV-1.
15. Positive ELISA and confirmatory tests for hepatitis C virus (HCV).
16. Positive hepatitis B surface antigen (HBsAg) by ELISA.
17. Pre-existing autoimmune or antibody-mediated diseases including but not limited to: systemic lupus erythematosus, rheumatoid arthritis, multiple sclerosis, Sjögren's syndrome, or autoimmune thrombocytopenia.
18. Known immunodeficiency syndrome.
19. Use of chronic ( $\geq 14$  days) oral or intravenous corticosteroids (excluding topical or nasal) at immunosuppressive doses (i.e. prednisone  $>10$  mg/ day) or immunosuppressive drugs within 30 days of starting this study.
20. Receipt of a live vaccine within past 4 weeks or a killed vaccine within past 2 weeks prior to entry into the study.
21. History of a surgical splenectomy.
22. Receipt of blood products within the past 6 months.
23. Previous receipt of an investigational malaria vaccine.
24. Refusal to allow storage of samples for future research.
25. Any medical, psychiatric, social, or occupational condition or other responsibility that, in the judgment of the Principal Investigator (PI), would interfere with the evaluation of study objectives.

## **5 Study Agent**

### **5.1 Vaccine**

The Pfs25-EPA/Alhydrogel® vaccine will be supplied to the study site pharmacist by the Pilot Bioproduction Facility, Walter Reed Army Institute of Research, [name] where the materials were formulated and packaged. Vaccines will be labeled for investigational use only.

### **5.2 Vaccine Administration**

The Pfs25-EPA/Alhydrogel® vaccine will be provided as a single-use vial. A 0.1 mL volume is administered for delivery of 8 µg conjugated Pfs25, a 0.2 mL volume is administered for delivery of 16 µg conjugated Pfs25, and a 0.6 mL volume is administered for delivery of 47 µg conjugated Pfs25. The vaccine can be drawn up into the syringe up to 5 hours prior to administration and will be mixed by hand before injection to ensure resuspension.

